**Table 17 Blood collection schedule for PK/PD measurement**

|                            | Before DC/Gal injection | Before iPS-NKT administration | Post-dose |     |     |
|----------------------------|-------------------------|-------------------------------|-----------|-----|-----|
| Time point (hour)          | —                       | —                             | 1         | 24  | 168 |
| Allowance (min)            | —                       | —                             | ±15       | ±30 | ±60 |
| Blood collection for PK/PD | —                       | ●                             | ●         | ●   | ●   |

### 7.1.1. Screening test

After obtaining consent, the screening tests are initiated. The PI or SI will perform the following screening tests and enroll patients who meet the selection criteria and do not violate the exclusion criteria. The test items shall be as described below.

- Body weight (usu. one's own)
- Vital signs
- ECOG PS
- Hematological examination
- Blood biochemical tests (including HbA1c)
- Coagulation test
- Urinalysis
- Pregnancy test (for women of childbearing potential only)
- Infectious disease test (HBs antigen, HBs antibody, HBc antibody, HCV antibody, HIV antibody or HTLV-1 antibody)
- 12-lead ECG test
- Chest X-ray
- Contrast-enhanced CT scan (vascular and tumor evaluation)
- HLA testing (up to area 2 by Luminex method)
- Anti-HLA antibody test

### 7.1.2. Subject Information

The following subject information should be recorded at the time consent is obtained or at the time of the screening test.

- 1) Date Consent was obtained
- 2) Subject Identification Code
- 3) Gender
- 4) Age
- 5) Stature
- 6) Previous history/complications
- 7) Diagnostic name
- 8) Organizational type
- 9) Staging
- 10) Body surface
- 11) Allergies

---

 Vital signs shall include temperature, pulse rate, respiratory rate, SpO2, and blood pressure (systolic and diastolic).

 Fujimoto formula (Body surface area (m^2) = Weight (kg)0.444 x Height (cm)0.663 x 88.83/10000) is used

12) Past cancer treatment and surgery

13) Alcohol and smoking history

### 7.1.3. Observation, test, assessment measurements

Blood Biochemistry Tests at each timing are listed below. In addition, vital signs and adverse events will be checked daily during the hospitalization period. Details of measurements are shown in Table 21. Additional tests (chest X-ray, hematological and serological tests, blood gas test, etc.) may be added as necessary for safety or other reasons at the discretion of the PI or SI.

**Table 18 List of laboratory test measurement**

|                                                                               |                                                                                                                                                                                                                                                                                                                                                                                                                                                                                                                                                                                                                                                                                                                                                                                      |
|-------------------------------------------------------------------------------|--------------------------------------------------------------------------------------------------------------------------------------------------------------------------------------------------------------------------------------------------------------------------------------------------------------------------------------------------------------------------------------------------------------------------------------------------------------------------------------------------------------------------------------------------------------------------------------------------------------------------------------------------------------------------------------------------------------------------------------------------------------------------------------|
| infectious disease test
(*only at screening)                               | HBs antigen, HBs antibody, HBc antibody, HCV antibody, HIV antibody or HTLV-1 antibody, or
HBV-DNA quantification (*Added when HBs antigen negative and HBs or HBc antibody positive)
HCV-RNA quantification (*Additional when HCV antibody positive)                                                                                                                                                                                                                                                                                                                                                                                                                                                                                                                          |
| HLA test
(*only at screening)                                              | HLA genes (HLA-A, B, C, DRB1, DQB1, DPB1)                                                                                                                                                                                                                                                                                                                                                                                                                                                                                                                                                                                                                                                                                                                                            |
| hematological examination                                                     | Red blood cell, hemoglobin, hematocrit, platelet count, white blood cell count, and Leukocyte fractions (neutrophils, lymphocytes, monocytes, eosinophils, basophils)                                                                                                                                                                                                                                                                                                                                                                                                                                                                                                                                                                                                                |
| Blood Biochemistry Test
(*HbA1c only at screening)                         | Total protein, albumin, total bilirubin, AST, ALT, ALP, LDH, BUN, creatinine, uric acid, Na, K, Cl, Ca, P, amylase, HbA1c                                                                                                                                                                                                                                                                                                                                                                                                                                                                                                                                                                                                                                                            |
| coagulation test                                                              | PT-INR, aPTT                                                                                                                                                                                                                                                                                                                                                                                                                                                                                                                                                                                                                                                                                                                                                                         |
| urinalysis                                                                    | pH, sugar, protein, urobilinogen, ketones, occult blood                                                                                                                                                                                                                                                                                                                                                                                                                                                                                                                                                                                                                                                                                                                              |
| Blood cytokine assay
(Using Bio-Plex Pro human cytokine GI 8-Plex A panel) | GM-CSF, IFN- $\gamma$ , IL-2, IL-4, IL-6, IL-8, IL-10, TNF- $\alpha$                                                                                                                                                                                                                                                                                                                                                                                                                                                                                                                                                                                                                                                                                                                 |
| Immuno-cell fractionation test                                                | T-cell count (cells/mL)
NK cell count (cells/mL)
NKT cells (cells/mL)
CD4+ T cell count (cells/mL)
CD8+ T cell count (cells/mL)
Naive CD4+ T cell count (cells/mL)
Central memory CD4+ T cell count (cells/mL)
Number of effector memory CD4+ T cells (cells/mL)
Number of effector CD4+ T cells (cells/mL)
Naive CD8+ T cell count (cells/mL)
Central memory CD8+ T cell count (cells/mL)
Number of effector memory CD8+ T cells (cells/mL)
Number of effector CD8+ T cells (cells/mL)
PD-1+ CD4+ T cell percentage (in CD4+CD3+ T cells)
PD-1+CD8+ T cell percentage (in CD8+CD3+ T cells)
PD-1+NKT cell percentage (% in NKT cells)
PD-1+ NK cell percentage (% in NK cells)
WBC count (pcs/mL)
Lymphocyte count (cells/mL) |
| Anti-HLA antibody test                                                        | Class I and II determination, Class I and II positive antibodies, DSA                                                                                                                                                                                                                                                                                                                                                                                                                                                                                                                                                                                                                                                                                                                |

#### 7.1.3.1. Cell preparation period (Day -7)

One week prior to DC/Gal administration, apheresis is performed after checking vital signs to create autologous DC/Gal.

#### 7.1.3.2. Treatment period

Before the injection of auto-DC/Gal on Day1, the following are performed

- Body weight
- Vital signs
- ECOG PS
- mMRC
- Hematological test
- Blood Biochemistry Test
- Urinalysis
- Immune cell repertoire analysis
- Confirmation that at least one month has passed since the previous treatment
- Tumor biopsy (optional)

Day 6, the following are performed before iPS-NKT cell administration

- Body Weight
- Vital signs
- ECOG PS
- mMRC
- Hematological test
- Blood Biochemistry Test
- Coagulation test
- Urinalysis
- Immune cell repertoire analysis※
- Anti-HLA antibody test
- PK/PD blood collection (1 hour after iPS-NKT administration)

Day6 (within 2 days after iPS-NKT administration) tumor biopsy (optional)

Day7 (24 hours after iPS-NKT cell administration) : PK/PD blood collection.

---

 Biopsies from tumors under topical or local anesthesia will be performed only on subjects who have been judged by the PI or SI to be able to perform the biopsy and who have given consent for the tumor biopsy.

Blood samples for immune cell repertoire analysis\* will be taken on Day 8.

The following will be performed on Day13.

- Body weight
- Vital sign
- Chest X-ray
- Hematological
- Blood Biochemistry Test
- Immune cell repertoire analysis※
- PK/PD

※Immune cell repertoire test: PBMCs are isolated from blood samples and stained for cell surface markers. Concentration and percentage of cancer-related immune cell fractions, mainly T cell fractions and NKT cell markers, in peripheral blood are calculated using flow cytometry.

- Adverse event evaluation  
(During the DLT evaluation period, if any disease or symptom is suspected to fall under the definition of DLT (see 5.2. Dose Limiting Toxicity (DLT)), the PI will immediately request the Independent Data Monitoring Committee to review the appropriateness of the decision and decide whether the study can continue in the patient.)

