#### 【Rationale】

- 1) When iPS-NKT cells are administered intravenously, they have been found to accumulate in the liver. In this study, iPS-NKT cells were administered intravenously into tumor-feeding arteries, and although it is expected that there will be little systemic circulation, the eventual effect on the liver cannot be ruled out, and therefore, this setting was determined based on consideration of the safety of the subjects.
- 2, 4-5) The iPS-NKT cells are intended for direct and indirect immune activation in the target patients and were set up to exclude the influence of diseases and drugs that affect the immune status of the target patients.
- 3) Since the effects of iPS-NKT cells on the fetus and fertility have not been confirmed to date, the dose was set to avoid such effects in the target population. Since iPS-NKT cells administered into the body are considered to be almost completely eliminated from the body on the seventh day after administration, a contraceptive period was established.
- 6-8) Considering the safety of the subjects.
- 9) This was established to exclude the impact of adverse events due to cancers other than head and neck. The time period was set based on the recurrence rate after curative treatment of gastrointestinal cancer, which is a particularly frequent overlapping cancer of the head and neck, and because the risk of recurrence is considered to be high within 2 years.
- 10) Since the use of contrast enhancements is mandatory in this study to confirm tumor-feeding arteries in the subject
- 11) Considering the subjects' safety
- 12) To exclude the effects by other experimental agent on other clinical trials.
- 13) Considering the PK/PD analysis, we need to detect the iPS-NKT cells with different genotype from subjects one.
- 14) Because it is impossible to conduct this study in patients who are unable to have component blood samples taken for DC/Gal preparation.
- 15) Other settings were made to allow for exclusions when the investigators judged that the study could not be safely conducted.

---

 The genotype of iPS-NKT cell used in this study is as follows:  
A\*26:01-B\*35:01-C\*03:03  
A\*26:03-B\*35:01-C\*03:03

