## 5. Study Method

### 5.1. Design

This is an open-label, single arm, Phase I study to evaluate the tolerability, safety, pharmacokinetics, pharmacodynamics, and antitumor effects of iPS-NKT cell in combination with auto-DC/Gal in patients with recurrent or advanced head and neck cancer who are refractory or intolerant to standard of therapy.

The dosing regimen involves both a submucosal injection of auto-DC/Gal at  $1.0 \times 10^8$  cells (fixed dose) followed by tumor-feeding arterial administration of the iPS-NKT cell at one of two dose levels: initial dose (first dose) cohort:  $3.0 \times 10^7$  cells/ $m^2$ , or second dose cohort:  $1.0 \times 10^8$  cells/ $m^2$ , administered at once, respectively. The iPS-NKT cell is administered at once five days after the DC/Gal injection. We avoid same-day administration of the investigational product to more than two subjects, and there must be a minimum interval of at least seven days before administering the investigational product to the following subject. We employed the three-by-three (3+3) design for dose escalation in this trial. Ultimately, the maximum tolerated dose (MTD) will be determined based on a total of six subjects with one or less DLT occurrences.

The screening period begins after obtaining the informed consent from each subjects. Based on the results of the screening tests, eligible subjects are registered in this study. One week prior to the start of study treatment, the subject's peripheral blood is collected, and auto-DC/Gal is manufactured (auto-DC/Gal preparation period).

DLT assessment period starts from the injection of auto-DC/Gal to 14 days after the iPS-NKT cell administration. During DLT assessment period, subjects will be carefully monitored under hospitalization. The PI or SI may leave the hospital at his/her own discretion only if the patient does not develop non-hematologic toxicity or hematologic toxicity of Grade 2 or higher and Grade 3 or higher on or after Day 7 of iPS-NKT cell administration, and be able to contact the study site and home doctor of the subjects, if any, in the event of an adverse event.

The Independent Data Monitoring Committee, consisting of members designated by the PI and study coordinating physicians, monitors the safety of the study and may make recommendations regarding the continuation of the study.

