## 5.2. Dose Limiting Toxicity (DLT)

DLT is defined as the following adverse events observed during the DLT assessment period, in which a causal relationship with auto-DC/Gal or iPS-NKT cell cannot be denied. Grading is determined according to the CTCAE ver.5.0 translated in Japanese by the Japan Clinical Oncology Group (JCOG).

- 1) Grade 4 or higher hematological toxicities
- 2) any non-disease-related blood toxicity requiring any transfusion or granulocyte-colony stimulating factor (G-CSF) administration
- 3) grade 3 or higher non-hematological toxicities (excluding transient clinical laboratory abnormalities, diarrhea, nausea, vomiting, or other manageable systemic symptoms that recovered to grade 2 or below under appropriate treatments)
- 4) AEs lead to blood transfusion.

If the PI suspects the occurrence of DLTs, the PI can consult the Independent Data Monitoring Committee (IDMC), and the IDMC determines the continuation or termination for the patient. Subjects who do not complete the DLT assessment period for reasons other than DLT will not be considered DLT evaluable cases and then another

subject will be supplemented in the same dose cohort.

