| DC/Gal preparation                        |   |            | ●            |                  |    |   |   |    |    |                                  |                 |    |             |
| DC/Gal injection                          |   |            |              | ●                |    |   |   |    |    |                                  |                 |    |             |
| iPS-NKT cell administration c) |   |            |              |                  | ●  |   |   |    |    |                                  |                 |    |             |
| CBC/Laboratory test                       |   | ●          |              | ●                | ●  |   |   | ●  |    | ●                                | ●               | ●  | ●           |
| Coagulation test                          |   | ●          |              |                  | ●  |   |   |    |    |                                  |                 |    |             |
| Urology                                   |   | ●          |              | ●                | ●  |   |   |    |    | ●                                | ●               | ●  | ●           |
| Vital sign d)                  |   | ●          | ●            | ←————→           |    |   |   |    |    |                                  |                 |    |             |
| Body weight                               |   | ●          |              | ●                | ●  |   |   | ●  |    | ●                                | ●               | ●  | ●           |
| ECOG PS                                   |   | ●          |              | ●                | ●  |   |   |    |    | ●                                | ●               | ●  | ●           |
| mMRC                                      |   |            |              | ●                | ●  |   |   |    |    |                                  |                 |    |             |
| PK/PD e)                       |   |            |              |                  | ●  | ● |   | ●  |    |                                  |                 |    |             |
| Immune cell assessment f)      |   |            |              | ●                | ●  |   | ● | ●  |    | ●                                |                 |    |             |
| AEs                                       |   | ←————→     |              |                  |    |   |   |    |    |                                  |                 |    |             |

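### No routine haematology or biochemistry panel is scheduled between the pre-dose sample on Day 6 and Day 13, so a brief, silent Grade 4 cytopenia after iPS-NKT, which is a DLT, can go unrecorded

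*Protocol*

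**What the plan says.** - **Dosing and window.** Section 5.1: "The iPS-NKT cell is administered at once five days after the DC/Gal injection", so with auto-DC/Gal on Day 1, iPS-NKT falls on Day 6. The same section states: "DLT assessment period starts from the injection of auto-DC/Gal to 14 days after the iPS-NKT cell administration".
- **Endpoint.** Section 5.2 lists "Grade 4 or higher hematological toxicities" as the first DLT criterion and sets no minimum duration. The non-haematological criterion (Grade 3 or higher) leaves out laboratory abnormalities that are transient. The other two criteria depend on a transfusion or on G-CSF being given.
- **Routine panels.** In the study calendar (captioned Table 16, cited as Table 19 in the text of 7.1), the row "CBC/Laboratory test" is marked within the treatment period on Days 1, 6 and 13, then on Observation Days 1, 15 and 28. It is blank on Days 7, 8 and 19. Section 7.1.3.2 agrees: the Day 6 list is introduced by "Day 6, the following are performed before iPS-NKT cell administration", and the next haematology and biochemistry come under "The following will be performed on Day13".
- **Other blood draws.** Section 7.1.3.2 has "Day7 (24 hours after iPS-NKT cell administration) : PK/PD blood collection" and an immune-cell sample on Day 8. The laboratory list in 7.1.3 shows that the immune-cell panel includes WBC and lymphocyte counts, but not neutrophils, haemoglobin, platelets or chemistry.
- **Other surveillance.** Section 7.1.3 provides for daily vital signs and adverse-event checks in hospital, and lets the investigator add blood tests when judged necessary.

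**The concern.** The primary endpoint includes a criterion that only a blood count can establish. A neutrophil or platelet nadir may cause no symptoms, and it qualifies as a DLT even if it lasts a day. iPS-NKT is the product whose dose is escalated, yet no routine panel follows it for a week. That is the week in which the protocol's own mouse data place most of the exposure: section 1.3.3 justifies the two-week window by blood levels down to 0.33% of the dose at 48 hours, and section 1.2.5.3 reports that the cells had gone from blood and organs by 96 hours in NOG mice. The first routine panel is at 7 × 24 = 168 hours. Exposure is not toxicity, but it is a reason to look early.

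Each dose is judged on three to six patients, and two DLTs stop escalation, so a single unrecorded event can change the decision. Laboratory change from baseline is also a secondary endpoint, and it has no routine value in the first post-dose week.

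**Working it through.** **1. Timeline, in days after iPS-NKT (calendar day minus 6)**

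| Calendar day | Days after iPS-NKT | Routine haematology and biochemistry | Other blood drawn |
|---|---|---|---|
| 6 | 0 | Yes, pre-dose | PK/PD before and 1 h after dosing; immune cells |
| 7 | +1 | No | PK/PD |
| 8 | +2 | No | Immune cells (WBC, lymphocytes) |
| 13 | +7 | Yes | PK/PD, immune cells |
| 19 | +13 | No | None marked |
| Observation Day 1 (per 5.1) | +14, i.e. Day 20, ±3 | Yes | Immune cells |

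The gap is 13 − 6 = 7 days, half of the 14 post-dose days in the window.

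**2. Illustration of scheduled detection.** Neither the duration nor the onset pattern is in the protocol; both are assumptions. Take an event lasting d = 3 days, onset uniform over days 0 to 14 after iPS-NKT, and no unscheduled tests. A sample at time t sees the event if onset lies between t − d and t.

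- Current schedule: the +7 sample sees onset in 4–7 and the +14 sample sees onset in 11–14. Detection = (3 + 3)/14 = 6/14 = 43%.
- With a full panel on Day 8 (+2): onset in 0–2 is added. Detection = (3 + 3 + 2)/14 = 8/14 = 57%.
- With a panel on Day 7 (+1) as well: onset in 0–1 is already seen at +2, so nothing is gained. Detection stays at 8/14.

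**3. Other durations, same model**

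| Duration (days) | Missed, panels at +7 and +14 | Missed, Day 8 added |
|---|---|---|
| 1 | 86% | 79% |
| 2 | 71% | 57% |
| 3 | 57% | 43% |
| 5 | 29% | 14% |
| 7 | 0% | 0% |

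For WBC and lymphocytes the last column already applies, because the Day 8 immune panel measures them.

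**4. The end of the window.** Section 5.1 puts the first observation day 14 days after iPS-NKT. Section 7.1.3.5 describes the first observation day as 28 days after iPS-NKT. The calendar allows ±3 days around Observation Day 1. If that panel fell at +17 or at +28, only the +7 sample would count towards a three-day event, and detection would be 3/14 = 21%. One possible reading is a labelling slip: if Observation Day 1 is at +14, then Observation Day 15, where 7.1.3.3 places the CT, is at 14 + 14 = +28. The text does not say so.

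**5. Sensitivity of the 3+3 rule.** A dose passes with probability (1 − p)³ + 3p(1 − p)⁵. For a true DLT rate of 0.33 this is 0.434 if every DLT is seen, 0.605 if 75% are seen and 0.783 if 50% are seen. The shares are assumed; the lower two would apply only if most DLTs were short-lived laboratory events.

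**The case against.** The calendar and the text agree on when panels are taken, so this is a choice of sampling frequency and not a contradiction. Patients are in hospital in principle throughout the window, vital signs and adverse events are checked daily, and extra tests are allowed. Laboratory abnormalities count as adverse events and are followed, and the IDMC makes the final DLT judgment. The single-dose toxicity study in section 1.2.4.1 found no haematological or biochemical abnormality. The reactions expected in section 1.2.7 (blood-pressure rise, fever, respiratory distress, shock and others) would be noticed at the bedside.

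Much of this stands, and it rules out several stronger readings that a reader might infer:

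- **That laboratory DLTs in general are lost.** A transaminase rise that resolves before Day 13 is the kind of transient change that section 5.2 excludes, so not counting it follows the definition. DLTs defined by transfusion or G-CSF leave a treatment record.
- **That the liver makes the gap more serious.** The rationale for the exclusion criteria says "When iPS-NKT cells are administered intravenously, they have been found to accumulate in the liver". But section 1.2.5.3 attributes the residual liver radioactivity to host cells, and its cell-sorter tables show none in BALB/c liver at 4 hours and at most 1 cell/g in NOG liver.
- **That Day 19 is a monitoring gap.** Under section 5.1 a full panel falls nominally one day later, and the continuous rows for vital signs, adverse events and DLTs may span the column. It is an orphan column to reconcile.
- **That no blood count at all is taken.** The Day 8 immune panel includes WBC and lymphocytes.
- **That testing the existing draws lifts detection from nothing to nearly everything.** That follows only if onset is assumed within 48 hours and duration fixed at three days.

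The objection does not reach a silent neutropenia or thrombocytopenia. Daily checks find symptoms and signs, and discretionary tests need a reason to be ordered; neither looks for a low count systematically.

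**Conclusion.** The point holds in a limited form. For the seven days after iPS-NKT, the schedule offers no neutrophil, haemoglobin, platelet or chemistry result. A brief, symptom-free Grade 4 cytopenia in that week meets the DLT definition and can go unrecorded. In the stated illustration, scheduled detection of a three-day event is 43% now and 57% with a Day 8 panel, a gain of 14 percentage points. The loss shrinks as events last longer and disappears at seven days, provided the end-of-window panel falls at +14.

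These figures describe the sampling schedule only. The protocol gives no rate, onset or duration of cytopenia for this product, so a material bias in the DLT rate, or a materially higher chance of escalating an unsafe dose, cannot be concluded from it. The change is still worth making: it closes an avoidable hole in the ascertainment of the primary endpoint at very little cost.

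**What to change.** 1. In Table 16 and section 7.1.3.2, add a CBC with differential and blood biochemistry to blood already drawn in the first 48 hours after iPS-NKT: the Day 8 draw, and optionally also Day 7. Day 8 is the one that adds detection in the three-day illustration.
2. Reconcile the Day 19 column, the two descriptions of the first observation day (14 days after iPS-NKT in section 5.1, 28 days in section 7.1.3.5) and the ±3-day allowance, so that one stated haematology and biochemistry panel closes the DLT window.

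The cost is routine tubes on one or two existing draws, a few mL more blood per patient, a calendar correction, and passage through the revision procedure in section 12.1. The observed DLT count may rise slightly because more events are seen.
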